### Study procedures

All secondary schools in Enfield, Lambeth and Southwark will be approached. Legal guardians (usually parents) from participating schools will be written to/emailed explaining the study and those not wishing to participate were asked to opt out to a school contact.

Schools randomised to the incentive intervention arm will be sent the intervention letter to give to students and teachers informed to tell students that they will be eligible for the incentive if their consent form is returned. At the same time, parents from schools in both arms will be asked by the immunisation team to consent to their daughter having the HPV vaccine as part of the routine programme, via an invitation letter, information leaflet and accompanying consent form. These standard immunisation programme materials are distributed to the girls by form tutors and their distribution/content is unaffected by the present study.

Following dose one of the vaccine being administered to those girls with consent, the research team will give the school administrative staff a list of unique anonymised identifiers to assign to each participating girl. The administrative team will add this list to an existing dataset containing all vaccine-eligible girls and the following information: an IMD score for each girl (derived from the girls’ postcodes), whether she returned a consent form and whether consent to vaccination was given on the consent form. Administrative staff will remove the girls’ names from the dataset and provide this to the researchers to take away from the school site.

Girls will be given a questionnaire to complete in the week after vaccination day by their form tutor, as well as a questionnaire pack to hand deliver to their parents. The parents’ packs will include a FREEPOST return envelope to send the questionnaires directly to researchers. Both questionnaires will be labelled with each girl’s unique identifier. Parents with more than one daughter in year eight will be asked to think of one child and respond about that child when completing the questionnaire. Girls will complete the questionnaire during a tutor group session. School staff will be invited to participate in a brief interview in an email sent from the research team via a member of the school administrative staff.

All interviews will be conducted shortly after vaccination day, either in person or on the phone by a member of the research team. Written/audio-recorded verbal informed consent will be taken by a member of the research team. They will be audio-recorded and transcribed verbatim.

### Sample size

This is a feasibility study and one of the outcomes will be to assess the willingness of the schools to take part in the study and to be randomised. We anticipate that at least six schools will agree to participate in the study based on our pilot work. On average, in participating boroughs, there are approximately 100 girls in year eight per school. With 600 girls, we will be able to estimate the binary feasibility outcomes (participation rates, questionnaire response rates and acceptability of the trial methods) with an unadjusted precision of the 95% confidence intervals to at least ±5 percentage points assuming the most statistically conservative scenario when the proportion is 0.5.

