## Methods/design

### Trial design

The trial design is a two-arm cluster randomised feasibility trial, with equal allocation to each arm (see Fig. 1).

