## Discussion

We have presented a protocol for a cluster randomised feasibility study of an adolescent incentive intervention to increase uptake of HPV vaccination among girls. The study will help provide the answers to questions required to design any main trial and whether it is appropriate to proceed with a future trial.

We have previously achieved high response rates to questionnaires completed by students in schools; however, response rates to questionnaires posted to parents are likely to be lower. Findings from this study will determine whether this approach to data collection from parents is likely to be successful in any main trial. We will also be able to observe if certain questionnaire items are often missing, suggesting that participants either did not understand them or did not find them relevant, allowing us to modify the questionnaires prior to any main trial. Interviews with school staff may also help to explain any missing data. Finally, we presently do not know if we will obtain more complete data on vaccination status by asking schools to record this data or by asking parents to report their daughter’s vaccination status. Findings of this feasibility study will suggest how best to collect data on vaccination status in any main trial.

The sample size is based on a conservative scenario and if achieved will allow us to estimate binary feasibility outcomes. For any main trial, a larger sample size will likely be required; this will be determined following this feasibility study. It is possible that schools participating in the feasibility study will be the most engaged in research. Further efforts may be required to recruit additional schools for any main trial and may require input from senior leadership to facilitate recruitment, such as local authorities. We have engaged with local authorities in the set-up of this feasibility study, so their input should be possible in any main trial.

Uptake of the HPV vaccine among eligible 12–13-year-old girls is sub-optimal in some populations. An incentive intervention to promote consent form return may result in improved uptake. This cluster randomised feasibility study will provide the evidence needed to decide if a future RCT testing the efficacy of such an intervention is feasible.

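### The ±5-point precision holds only unadjusted for clustering and only for outcomes with about 600 individual units; with six schools it needs an ICC of about 0.006 or less at p = 0.5

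*Protocol article*

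**What the plan says.** The design is a "two-arm cluster randomised feasibility trial, with equal allocation to each arm" (Protocol article, Trial design), with the school as the unit of allocation.

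The Sample size section gives the inputs: "We anticipate that at least six schools will agree to participate in the study" and "there are approximately 100 girls in year eight per school". It continues: "With 600 girls, we will be able to estimate the binary feasibility outcomes", naming participation, questionnaire response and acceptability of the trial's methods. The precision claimed is "an unadjusted precision of the 95% confidence intervals to at least ±5 percentage points", "assuming the most statistically conservative scenario when the proportion is 0.5".

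The Discussion returns to this: "The sample size is based on a conservative scenario and if achieved will allow us to estimate binary feasibility outcomes". There, neither the word unadjusted nor the link to p = 0.5 is carried over.

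The Outcomes and Statistical methods sections show what the listed outcomes are. Participation includes the share of approached schools that join, as well as the share of parents who opt out. Response rates have the girls given, and the parents sent, a questionnaire as their denominators.

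**The concern.** The girls arrive as about six whole year groups, but the precision is that of 600 independent girls. Responses within a school may well be alike. Under Study procedures, form tutors hand out the questionnaires, girls complete them in tutor-group sessions, and parents opt out through a school contact. Response may therefore depend partly on how each school runs the process. In that case 600 girls carry less information than 600 independent observations.

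The same figure is attached to outcomes that do not have 600 units. School participation is counted in schools. Acceptability judged by questionnaire is counted in respondents, and acceptability judged by staff interview is counted in staff.

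Estimating design parameters is a stated purpose of the study, and this sentence is the document's only quantitative justification of its size. If a response rate is reported and used as though known to within 4 or 5 points when six schools support something nearer 7 to 13, the main trial will be planned on more certainty than the data hold.

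**Working it through.** **Inputs from the protocol article (Sample size):** 6 schools as a minimum, about 100 girls each, n = 600, p = 0.5, 95% interval.

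**Assumptions, not in the document:** the ICC (0.01 to 0.10 tabulated), the number of schools approached (20 to 60) and the questionnaire response (30% or 50%).

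**1. The plan's own figure.** Half-width = 1.96 × √(p(1 − p)/n) = 1.96 × √(0.25/600) = ±4.0 points. This is inside the stated ±5, so the claim is reproduced with margin.

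**2. How much clustering ±5 tolerates.** An unadjusted ±5 needs n = 1.96² × 0.25/0.05² = 384.1, that is 385. The largest tolerable design effect is 600/384.1 = 1.56. With the design effect equal to 1 + (m − 1) × ICC and m = 100, the ICC limit is (1.56 − 1)/99 ≈ 0.0057.

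**3. Half-width with clustering**, p = 0.5, 6 × 100 girls. The z column is 1.96 × √(0.25 × DE/600). The t column replaces 1.96 by 2.571 (5 df, six schools).

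| Assumed ICC | Design effect | Effective n | z (points) | t, 5 df (points) |
|---|---|---|---|---|
| 0 | 1.00 | 600 | ±4.0 | ±5.25 |
| 0.01 | 1.99 | 302 | ±5.6 | ±7.4 |
| 0.02 | 2.98 | 201 | ±6.9 | ±9.1 |
| 0.05 | 5.95 | 101 | ±9.8 | ±12.8 |
| 0.10 | 10.9 | 55 | ±13.2 | ±17.3 |

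**4. Away from p = 0.5 (z).** At p = 0.8: ±4.5 for ICC 0.01 and ±7.8 for ICC 0.05. At p = 0.9: ±4.1 for ICC 0.02 and ±5.9 for ICC 0.05. At p = 0.9 the tolerable ICC rises: n needed = 1.96² × 0.09/0.05² = 138.3, design effect 600/138.3 = 4.34, ICC (4.34 − 1)/99 ≈ 0.034.

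**5. School participation.** The unit is the school. At p = 0.5, 1.96 × √(0.25/k) gives ±21.9 for k = 20 approached, ±15.5 for 40 and ±12.7 for 60. If exactly six join, so that p = 6/k, the half-widths are ±20.1, ±11.1 and ±7.6. None reaches ±5.

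**6. Acceptability from questionnaires.** The unadjusted ±5 needs 385 of 600 respondents, or 64%. At 50% response (n = 300) it is ±5.7, and at 30% (n = 180) ±7.3, before clustering. At 50% response and ICC 0.05 the design effect is 1 + 49 × 0.05 = 3.45, giving 1.96 × √(0.25 × 3.45/300) = ±10.5.

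**The case against.** The strongest reply is that the protocol makes no arithmetic error and hides nothing. It says the figure is unadjusted, and as such it is true with a point to spare. In the Sample size section the word conservative is tied expressly to p = 0.5, which is correct. Parental opt-out and both response rates do have about 600 units. All of this stands.

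It also stands that the size of the shortfall depends on an ICC the document does not give. A reader might infer that ±5 will not be achieved. That goes too far: a very small ICC, a proportion far from 0.5 (the Discussion reports high student response in earlier work) or more than the minimum of six schools would each narrow the interval. Part of the gap in the t column comes from the reference distribution, since it exceeds ±5 even at ICC 0.

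Two further inferences are tempting and unsupported.
- The borough uptakes in the Setting section (75%, 82%, 83%) might be turned into an ICC. They vary between boroughs, not schools, and they concern vaccine uptake, which is not among the outcomes the precision is claimed for.
- Attitudes to the incentive might be counted on one arm of about 300 girls. The precision is claimed for acceptability of the trial's methods, which the Objectives separate from acceptability of the intervention. Nothing says that the attitude items go to one arm only.

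Finally, nothing shows that naive intervals will be reported. The analysis is mainly descriptive, interval methods may be set out in an analysis plan that is not shown, and progression has no numerical threshold. This lowers the stakes. It does not rescue the precision statement, because disclosing that clustering is left out does not tell the reader what precision the chosen design has.

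**Conclusion.** The concern holds in a limited form. The ±5 is correct as an unadjusted figure for outcomes with about 600 individual units. As a description of what about six schools can deliver at p = 0.5, it requires an ICC of at most about 0.006 on a z basis. For assumed ICCs of 0.02 to 0.10 the half-width is about ±6.9 to ±13.2 points, wider on 5 df and narrower for proportions near 0 or 1 or with more schools. It cannot apply to school participation at p = 0.5 for any plausible number of schools in three boroughs, and it applies to questionnaire-based acceptability only with at least 385 respondents and negligible clustering. The Discussion's unqualified description of the basis as conservative overstates it, because treating girls within schools as independent works in the opposite direction.

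The conclusion rests on equal schools of about 100 and on assumed ICCs, response levels and numbers of schools approached. Severity is moderate: the study tests no hypothesis, and no progression rule turns on an interval.

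**What to change.** - **Sample size:** keep the unadjusted figure if wished, but add the clustered range. For example: with six schools of about 100 girls and a proportion of 0.5, the 95% half-width is about ±6.9 to ±13.2 points for assumed ICCs of 0.02 to 0.10. Say that the ICCs are assumptions.
- **Denominators:** limit the 600-girl statement to parental opt-out and the two response rates. Give school participation its own precision, based on the number of schools approached. Give questionnaire-based acceptability a precision based on the expected number of respondents.
- **Reporting:** allow for school in any girl- or parent-level 95% interval that is published. The choice of method can be left to the analysis plan.
- **Discussion:** state that conservative refers only to p = 0.5 and that the figure ignores clustering.

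The cost is a less favourable stated precision and a few lines of analysis. No extra schools are needed. Recruitment ended on 15 December 2016 (Trial status), so the change bears on how results are reported and carried into the main trial's design.

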### Allocation

Blocked randomisation will be performed by the statistical advisor using computer generated random numbers. The statistical advisor will place pre-generated randomisation lists on a list of participating schools (with names concealed) and will send school allocation to the study research assistant. The research assistant will inform participating schools of their group assignment.

### Blinding

Once allocated (and information materials sent to schools allocated to the incentive intervention arm), group allocation will be kept separately from the main dataset. Trial arms will be labelled “A” and “B” in the dataset by the statistical advisor, who will keep the key and the main analyst will be blind to the group allocation until analysis is complete. Participants will not be blind to the group allocation.

### Data management

Data will be input by a research assistant, with 10% of data entered from questionnaires checked. If accuracy is <100%, a further 10% of data entered will be checked, with the process repeated until no errors are identified. Errors will be corrected. No identifiable data will leave school sites. Interview transcripts will be fully anonymised.

### Statistical methods

As this is a feasibility study our primary focus will be on assessing the outcomes regarding trial procedures, data quality and estimates of design parameters. The analysis for the feasibility outcomes will be primarily descriptive. School characteristics will be presented by arm. Data are available on participating and non-participating schools regarding school size, whether schools are single sex/mixed, and HPV vaccine uptake in the previous year. Participating and non-participating schools will be compared descriptively based on these factors to examine how representative participating schools are of their respective boroughs. Participant characteristics at baseline will be presented overall, by arm and by school. We will estimate and report on the proportion of schools approached that participate, the proportion of parents approached who opt out of the study, the proportion of parents sent a questionnaire who return the questionnaire and the proportion of girls given a questionnaire who complete the questionnaire.

We will estimate and report on the proportion of missing data for consent form return rates, vaccination consent, girls’ IMD score and all questionnaire items.

Acceptability of the incentive among girls and parents will be assessed descriptively. Interviews will be analysed descriptively to assess the range of opinions.

Parents’ mean informed decision-making scores will be presented by cluster and by trial arm, as will the data for other unintended consequences and mechanisms of action. We will summarise by cluster and by trial arm, the proportion of girls whose parents consent to the vaccine and the proportion of consent forms returned.

The trial will be reported according to the CONSORT extension to cluster randomised trials, CONSORT extension to randomised pilot and feasibility trials and this protocol has been prepared using the SPIRIT guideline [47–49].

### Missing data

The proportion of missing data for each variable collected via questionnaire will be reported. In line with Carpenter and Kenward [50], during a blind review of the data, the lead analyst and the statistical advisor will meet to decide upon the most appropriate missing data model and will apply this prior to analysis.

### Economic evaluation

Cost per returned consent form and cost per consent form agreeing to vaccination will be defined as the total unit cost of all consumables and incentive where relevant, divided by the number of consent forms returned or the number of consent forms returned that are agreeing to vaccination (following the method of Woodhall et al. [51]).

Interviews will be conducted with HPV-related cancer prevention stakeholders to identify the long-term cost implications of the intervention, including the administration of the incentive. This preparatory work will inform the economic analysis conducted as part of the future RCT.

### Monitoring

A trial management group comprising the study team will meet at the beginning and end of the study and throughout as needed. A data monitoring committee was not deemed necessary for this feasibility study. There will be no interim analyses or stopping guidelines. All members of the study team will have access to the final dataset. We do not anticipate any adverse events, but unintended consequences of the intervention are being measured. Immunisation teams and school staff will have a contact within the research team to report any adverse events.

### Deciding to proceed to a full trial

The decision to proceed to a definitive trial will be a multifaceted one, based on the trial procedures being acceptable to participants/stakeholders and feasible to deliver and scale up.

### Ethics and dissemination

Ethical approval has been received from the UCL Research Ethics Committee (6615/002). Modifications to this protocol will be communicated to relevant parties by the principal investigator. Results will be published in a peer review journal and presented at conferences.

## Discussion

We have presented a protocol for a cluster randomised feasibility study of an adolescent incentive intervention to increase uptake of HPV vaccination among girls. The study will help provide the answers to questions required to design any main trial and whether it is appropriate to proceed with a future trial.

We have previously achieved high response rates to questionnaires completed by students in schools; however, response rates to questionnaires posted to parents are likely to be lower. Findings from this study will determine whether this approach to data collection from parents is likely to be successful in any main trial. We will also be able to observe if certain questionnaire items are often missing, suggesting that participants either did not understand them or did not find them relevant, allowing us to modify the questionnaires prior to any main trial. Interviews with school staff may also help to explain any missing data. Finally, we presently do not know if we will obtain more complete data on vaccination status by asking schools to record this data or by asking parents to report their daughter’s vaccination status. Findings of this feasibility study will suggest how best to collect data on vaccination status in any main trial.

The sample size is based on a conservative scenario and if achieved will allow us to estimate binary feasibility outcomes. For any main trial, a larger sample size will likely be required; this will be determined following this feasibility study. It is possible that schools participating in the feasibility study will be the most engaged in research. Further efforts may be required to recruit additional schools for any main trial and may require input from senior leadership to facilitate recruitment, such as local authorities. We have engaged with local authorities in the set-up of this feasibility study, so their input should be possible in any main trial.

Uptake of the HPV vaccine among eligible 12–13-year-old girls is sub-optimal in some populations. An incentive intervention to promote consent form return may result in improved uptake. This cluster randomised feasibility study will provide the evidence needed to decide if a future RCT testing the efficacy of such an intervention is feasible.

### Trial status

Recruitment started on 1 July 2016 and ended on 15 December 2016.

## Abbreviations

BAME: Black and Asian Minority Ethnic
CI: Confidence interval
HPV: Human papillomavirus
IMD: Index of Multiple Deprivation
NHS: National Health Service
RCT: Randomised controlled trial
UCL: University College London
